## Abstract

**Rationale:** Early evidence for the benefit of mechanical thrombectomy (MT) in pediatric patients with intracranial large vessel occlusion has been shown in previous retrospective cohorts. Higher-level evidence is needed to overcome the limitations of these studies such as the lack of a control group and the retrospective design. Randomized trials will very likely not be feasible, and several open questions remain, for example, the impact of arteriopathic etiologies or a possible lower age limit for MT. Save ChildS Pro therefore aims to demonstrate the safety and effectiveness of MT in pediatric patients compared to the best medical management and intravenous thrombolysis.

**Design:** Save ChildS Pro is designed as a worldwide multicenter prospective registry comparing the safety and effectiveness of MT to the best medical care alone in the treatment of pediatric arterial ischemic stroke (AIS). It will include pediatric patients (<18 years) with symptomatic acute intracranial arterial occlusion who underwent either MT or best medical treatment including intravenous thrombolysis.

**Outcomes:** The primary endpoint of Save ChildS Pro is the modified Rankin Scale score at 90 days post-stroke. Secondary endpoints will comprise the decrease of the Pediatric National Institutes of Health Stroke Scale score from admission to discharge and rate of complications.

**Discussion:** Save ChildS Pro aims to provide high-level evidence for MT for pediatric patients with AIS, thereby improving functional outcome and quality of life and reducing the individual, societal, and economic burden of death and disability resulting from pediatric stroke.

**Clinical Trial Registration:** Save ChildS Pro is registered at the German Clinical Trials Registry (DRKS; identifier: DRKS00018960).

## Introduction

Arterial ischemic stroke (AIS) affects 1.3 to 1.6 per 100,000 children every year in developed countries (1–3), and outcomes are potentially severe, with 70% retaining long-term neurological deficits, 20% suffering recurrent strokes, and 10% of strokes resulting in death of the child (4–6). Risk factors for adult stroke such as atherosclerosis are nearly non-existent in pediatric stroke, so that knowledge and evidence of adult stroke cannot be extrapolated to children. Moreover, a lack of recruitment led to the termination of the prospective randomized TIPS (Thrombolysis in Pediatric Stroke) trial designed to assess the safety of intravenous tissue-type plasminogen activator (iv-tPA) in pediatric patients, highlighting the challenges of randomizing children with acute stroke (7). For mechanical thrombectomy (MT) in adults, several randomized clinical trials published in 2015 have shown the efficacy and safety of endovascular recanalization for large vessel occlusions (LVOs) with large effect size (8). In children, after several case series (9, 10), the retrospective Save ChildS Study recently provided the first systematic evidence for the safety of MT in children (11–13). In this study, the rate of recanalization and adverse events was comparable to large randomized controlled trials in adults, and neurological outcomes of the children were generally favorable. However, definitive conclusions cannot be drawn given the limitations of the Save ChildS Study, which include the lack of a control group of LVO patients not treated by MT and the retrospective design (14). Important questions remain, such as a possible lower age limit to perform thrombectomy in children or the impact of specific etiologies such as cerebral arteriopathies on the safety and efficacy of MT.

With the abovementioned difficulties in recruiting pediatric stroke patients for randomized controlled trials together with the ethical concerns about randomizing children into a non-MT group on the basis of the current knowledge, prospective randomized trials on MT in children are unlikely to succeed. Therefore, a prospective multicenter registry is considered the best option to collect further evidence for performing interventional recanalization in childhood stroke (14, 15).

The primary objective of the Save ChildS Pro registry is therefore to generate evidence for the use of MT in childhood stroke under the hypothesis that MT is safe and results in a high rate of good clinical outcomes compared to the best medical treatment including intravenous thrombolysis. The Save ChildS Pro registry further serves the purpose of defining selection criteria for MT in pediatric patients, especially for potentially vulnerable subgroups such as very young children, children with AIS due to arteriopathy, and children in the late therapeutic window.

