### Secondary Outcomes

Secondary endpoints will comprise the decrease of the Pediatric National Institutes of Health Stroke Scale (PedNIHSS) score from admission to discharge and rate of complications. The study will undergo an interim analysis after the first 50 patients have been enrolled.

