##### 24 h

PedNIHSSImaging findings (persistent or new occlusion, type of follow-up imaging, ASPECTS)Adverse events (symptomatic ICH, non-symptomatic ICH, dissection, other)

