### Statistical Analyses

Summary tables for patient demographics and baseline characteristics will be provided, and comparisons will be made between study arms for the endovascular and best medical treatment groups. The primary and secondary outcomes will be summarized and compared between study groups for the endovascular and best medical treatment groups.

In general, summaries will be presented by occlusion location within treatment group in the relevant analysis populations. Descriptive statistics for dichotomous/categorical variables will include the number and percent of subjects in each category (including missing), by treatment group. Descriptive statistics for continuous variables will include the number of non-missing and missing variables, minimum, lower quartile, median, upper quartile, maximum, mean, and standard deviation, stratified by treatment group. Regarding comparisons between treatment groups, χ^2^ test (Fisher exact test where appropriate) will be utilized for the comparison of categorical variables, and the *t* test (or the Mann–Whitney *U*-test when appropriate) will be utilized for the comparison of continuous variables. Data for the primary outcome will be presented by treatment group. Confidence intervals for dichotomous or ordinal endpoints will be reported on the odds ratio scale.

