## Conclusion

Save ChildS Pro is a worldwide multicenter prospective registry to compare the safety and effectiveness of endovascular thrombectomy to the best medical care alone (including intravenous thrombolysis) in the treatment of pediatric AIS. Save ChildS Pro will provide high-level evidence regarding effectiveness and safety of thrombectomy for pediatric AIS, improving the ability to determine which children are likely to benefit from this therapy.

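### The safety aim is paired only with tests of no difference and odds-ratio intervals, which cannot support it when complications are rare and groups are small

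*Protocol article*

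**What the plan says.** The Abstract says that the registry "aims to demonstrate the safety and effectiveness of MT in pediatric patients compared to the best medical management and intravenous thrombolysis". The Introduction places safety inside the primary objective, "under the hypothesis that MT is safe and results in a high rate of good clinical outcomes", again with best medical treatment as the comparator. The Conclusion says that the registry "will provide high-level evidence regarding effectiveness and safety of thrombectomy for pediatric AIS".

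Safety is measured under Secondary Outcomes, which name the decrease in the PedNIHSS "score from admission to discharge and rate of complications". The assessment lists record events by type. At 24 h the entry is "Adverse events (symptomatic ICH, non-symptomatic ICH, dissection, other"; the discharge and day 90 lists add hemicraniectomy and external ventricular drainage, and day 90 also adds pneumonia and recurrent stroke.

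Statistical Analyses names the chi-square test ("Fisher exact test where appropriate) will be utilized for the comparison of categorical variables") and says: "Confidence intervals for dichotomous or ordinal endpoints will be reported on the odds ratio scale". It also plans counts and percentages by treatment group. The only patient number in the article is in Secondary Outcomes: "The study will undergo an interim analysis after the first 50 patients have been enrolled".

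**The concern.** A test of no difference can reveal harm, but its failure to reject is not evidence of safety. That matters most for events that are serious and infrequent, such as symptomatic intracerebral hemorrhage (ICH), where the test may have little chance of detecting even a large excess.

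The chosen effect scale adds to this. When the medical arm has no events, the sample odds ratio is infinite and its interval is open at the top, which is the side that matters for safety. The interval then cannot say how large an excess of harm remains compatible with the data. A risk difference can.

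At stake is the safety statement of a pediatric registry that expects to inform which children receive an invasive treatment.

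**Working it through.** **Inputs from the article.** The comparison is MT against best medical treatment, the test is chi-square or Fisher, the effect scale is the odds ratio, and an interim analysis takes place at 50 patients. The article has no power, alpha, event rate or final sample size, so there is no stated figure to reproduce.

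**Assumptions.** Two-sided alpha 0.05; equal groups; medical-arm rates of 1%, 2%, 5% and 10%, tripled under MT; 25 to 200 per arm. The 25-per-arm case is the interim analysis if it splits evenly.

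**Step 1. Power of the Fisher test.** Power is the sum, over all pairs of event counts for which the Fisher p-value is at most 0.05 and the MT rate is the higher one, of Bin(x; n, p_med) × Bin(y; n, p_MT).

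| Medical vs MT | 25 per arm | 50 | 100 | 200 |
|---|---|---|---|---|
| 1% vs 3% | 0.0% | 0.2% | 3.4% | 16.9% |
| 2% vs 6% | 0.2% | 3.2% | 17.1% | 44.0% |
| 5% vs 15% | 7.2% | 24.4% | 58.6% | 90.5% |
| 10% vs 30% | 30.5% | 64.0% | 93.5% | 99.9% |

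The uncorrected chi-square test is somewhat more powerful: at 100 per arm it gives 14.1%, 27.6%, 68.3% and 95.6% for the four rows. Unequal groups do not change the pattern. For 5% against 15%, Fisher power is 74.7% with 100 medical and 200 MT patients, and 79.0% with the numbers reversed.

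**Step 2. Chance of no events in the medical arm.** This is (1 − p)^n.

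| Medical rate | 25 | 50 | 100 |
|---|---|---|---|
| 2% | 0.98^25 = 60% | 36% | 13% |
| 5% | 0.95^25 = 28% | 8% | 0.6% |
| 10% | 0.90^25 = 7% | 0.5% | about 0% |

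**Step 3. What each scale reports.** The Newcombe interval for the difference d = p1 − p2 uses the Wilson limits (l, u) of each arm: lower limit d − √[(p1 − l1)² + (u2 − p2)²], upper limit d + √[(u1 − p1)² + (p2 − l2)²].

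- *3/50 MT vs 0/50 medical.* The exact 95% interval for the odds ratio is 0.42 to infinity. The Wilson limits are 2.06% to 16.22% and 0% to 7.13%. In percentage points, d = 6, lower limit 6 − √(3.94² + 7.13²) = −2.1, upper limit 6 + √(10.22² + 0²) = 16.2. The odds-ratio interval sets no upper bound; the risk difference bounds the excess at about 16 points.
- *3/50 vs 1/50.* Fisher p = 0.62. The exact odds-ratio interval is about 0.24 to 167. The Wilson limits for 1/50 are 0.35% to 10.50%, so d = 4, lower limit 4 − √(3.94² + 8.50²) = −5.4, upper limit 4 + √(10.22² + 1.65²) = 14.3. The test is far from significant, yet an excess of 14 points is not excluded.
- *5/25 vs 0/25, which needs no assumed event rate.* Fisher p = 0.0502. An observed 20% against 0% at the interim size would be non-significant, with an infinite sample odds ratio.

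**The case against.** Several points on the other side stand.

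- A reader might infer that the registry will take a non-significant test as proof of safety. The article does not say so. Statistical Analyses names its tests for categorical variables in general and gives no rule for reading any of them.
- A reader might also infer that a non-significant result is near certain whatever the truth. That does not follow. The article gives neither event rates nor a final sample size, 50 centers had agreed to take part, and the number of sites is not limited. Step 1 shows good power once events are less rare or groups larger.
- Rarity is itself an assumption. The endpoint could pool many event types, including asymptomatic hemorrhage and vasospasm, and the pooled rate could be substantial.
- Each arm's counts and percentages are already planned, and so are intervals. An odds-ratio interval of 0.24 to 167 does not hide the uncertainty.
- Zero events do not make the odds ratio wholly uninformative, because the exact lower limit stays finite. For 6/100 against 0/100 it is 1.21, with p = 0.029.
- A safety margin and a sample size may stand in the full protocol or analysis plan, so their absence from an article is no fault.

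What remains is narrower. The article does fix a test family and an effect scale for dichotomous endpoints. For rare complications in small groups, neither answers the safety question that the article sets itself.

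**Conclusion.** The concern holds in a limited form. The aim of demonstrating safety is matched with methods that can detect harm but whose null result cannot support safety, and with an effect scale that loses its upper limit when the medical arm has no events.

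The weakness is severe for rare events at the interim size: Fisher power is at most about 7% for a tripling from 5% or less at 25 per arm, and the medical arm has no events with probability 28% at a 5% rate and 60% at 2%. It fades as rates or numbers rise; at 100 per arm, power is 59% from a 5% rate and 93% from 10%. All these figures rest on the assumed rates, equal groups and two-sided 0.05.

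This is a cheap improvement to a stated method. It does not show that the registry's safety result will be uninformative.

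**What to change.** In Statistical Analyses, for individual complications (symptomatic ICH, any ICH, death, recurrent stroke):

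1. Report each arm's rate with an exact 95% confidence interval, and the risk difference with a Newcombe or score 95% interval. Give these alongside the odds ratio, or in its place when a cell is zero.
2. State that the safety statement rests on the upper limit of the risk-difference interval. Describe that limit as the excess compatible with the data, subject to confounding, because treatment is not randomized.
3. State that a non-significant test will not be reported as showing safety, and align the wording of the safety aim in the Introduction with this.

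The upper limit does not by itself declare MT safe; that would need an acceptable excess fixed in advance, and this change does not depend on one. The cost is a few sentences and one table format, with no new data. The downside is a less favorable safety statement while numbers are small.

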## Methods

### Design

Save ChildS Pro is a worldwide multicenter prospective registry that aims to compare the safety and effectiveness of MT to the best medical care alone (including intravenous thrombolysis) in the treatment of pediatric AIS. As of January 2020, 50 centers in nine countries (Germany, Switzerland, Austria, Italy, Sweden, United States, Australia, Argentina, Canada) have agreed to participate. Patient data will be entered through a web-based interface (Eppdata).

Save ChildS Pro is registered at the German Clinical Trials Registry (DRKS; identifier DRKS00018960) and has been approved by the ethics committee of the University of Muenster, Muenster, Germany, in accordance with the Declaration of Helsinki, with waiver of informed consent due to anonymization of the submitted data.

### Patient Population

Patients presenting with AIS from January 1, 2020, will be considered for prospective study enrolment.

The following inclusion criteria apply:

clinical diagnosis of acute ischemic strokeconfirmed diagnosis of arterial occlusion consistent with symptoms, including occlusion of terminal carotid artery, middle cerebral artery (M1, M2, M3 segments), basilar artery, anterior cerebral artery (A1, A2 segments), or posterior cerebral artery (P1, P2 segments)endovascular treatment (EVT) attempted (i.e., groin puncture initiated, including all cases where EVT failed or was interrupted) or best medical treatment including intravenous thrombolysisage <18 years

The following is the exclusion criterion:

perinatal stroke

### Study Groups

#### Endovascular Group

Patients treated with MT (i.e., groin puncture initiated, including all cases where EVT failed or was interrupted), according to established clinical practice, belong to the endovascular group.

#### Best Medical Treatment Group

The best medical treatment group includes patients who are treated with best medical therapy (including systemic thrombolysis), according to established clinical practice.

## Outcomes

### Primary Outcomes

The primary endpoint of Save ChildS Pro is the patient's modified Rankin Scale score (mRS) at 90 days post-stroke assessed with a shift analysis.

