#### Study Design

Non-interventional, open-label, prospective, multicenter, observational registry study.

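### The stated primary comparison of raw day-90 mRS ignores the pre-stroke mRS that the registry collects: prior disability modestly attenuates the shift effect and, if unequal between the groups, biases it in either direction.

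*Protocol article*

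**What the plan says.** All references are to the Protocol article.

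- **Endpoint (Primary Outcomes).** The primary endpoint is the "modified Rankin Scale score (mRS) at 90 days post-stroke assessed with a shift analysis". It is not referenced to the child's level before the stroke, and no cut-off for a good or poor outcome is given.
- **Eligibility (Patient Population).** Children enter on stroke diagnosis, a confirmed matching occlusion, treatment and age. The list of exclusions opens with "The following is the exclusion criterion", in the singular, and names perinatal stroke only.
- **Data collected (Admission).** Pre-existing diseases are recorded. So is an mRS headed as the admission score, with a bracket explaining that it refers to deficits present before the stroke.
- **Analysis (Statistical Analyses).** Baseline variables have a descriptive role: "Summary tables for patient demographics and baseline characteristics will be provided, and comparisons will be made between study arms". For differences between the treatment groups, categorical variables are compared by χ² or Fisher tests, and "the *t* test (or the Mann–Whitney *U*-test when appropriate) will be utilized for the comparison of continuous variables". On the effect scale: "Confidence intervals for dichotomous or ordinal endpoints will be reported on the odds ratio scale". No covariate or stratification by pre-stroke status is named for the outcome comparison.
- **Design (Study Design).** "Non-interventional, open-label, prospective, multicenter, observational registry study". Both treatment groups are defined by established clinical practice.

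**The concern.** A child who lived at mRS 3 before the stroke and recovers from it completely would still be expected to score 3 at day 90. The raw score therefore mixes old disability with the result of the stroke. This has two consequences.

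1. **Attenuation.** Even if prior disability is equally common in both groups, part of the scale is closed to these children. The common odds ratio moves towards 1.
2. **Bias.** Nothing in the design balances prior disability between the groups. If it is unequal, the unadjusted odds ratio departs from the true one, in favour of whichever group has less of it.

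The primary comparison of MT with medical treatment is exposed to both, and the variable that would address them is already on the data list.

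**Working it through.** **No figure to reproduce.** The article states no sample size, effect size, mRS distribution or prevalence of prior disability. Everything below is an illustration on assumed inputs.

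**Assumptions**
- Stroke-related mRS 0 to 6 under medical treatment: 15/20/20/15/10/10/10%.
- Day-90 mRS = max(pre-stroke mRS, stroke-related mRS).
- A share f of each group has pre-stroke mRS 3; the rest have no prior disability.
- True common odds ratio (OR) for a better score with MT: 2.0 or 1.0.
- Observed OR: a proportional-odds model fitted by maximum likelihood to the expected distributions, with equal group sizes.

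**Step 1: what the floor does at each cut of the scale.** Below the floor, P(mRS ≤ j) is multiplied by (1 − f). At or above it, nothing changes.

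Equal f = 20%, true OR 2.0:
- Cut 0–2, medical: 0.80 × 0.55 = 0.440, odds 0.786.
- Cut 0–2, MT: stroke-related odds 2 × 0.55/0.45 = 2.444, probability 0.710; 0.80 × 0.710 = 0.568, odds 1.313.
- OR at this cut: 1.313/0.786 = 1.67 instead of 2.0.
- Cut 0–3: odds 0.70/0.30 = 2.333 against 4.667, so the OR is still 2.0.

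The loss is confined to the cuts below the floor. Among children with pre-stroke mRS 3, the share ending no worse than 3 still rises from 70% to 4.667/5.667 = 82%.

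**Step 2: equal prevalence, true OR 2.0**

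| f in both groups | Unadjusted OR | OR with prior disability as additive covariate |
|---|---|---|
| 5% | 1.95 | 1.97 |
| 10% | 1.91 | 1.95 |
| 20% | 1.83 | 1.90 |

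At f = 20% the covariate recovers (1.90 − 1.83)/(2.00 − 1.83) = 0.07/0.17, or about 40% of the attenuation.

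**Step 3: unequal prevalence, no treatment effect (true OR 1.0)**

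| f medical | f MT | Unadjusted OR | Adjusted OR |
|---|---|---|---|
| 5% | 2% | 1.04 | 1.00 |
| 10% | 5% | 1.06 | 1.00 |
| 20% | 5% | 1.20 | 1.00 |
| 5% | 20% | 0.84 | 1.00 |

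Hand check of the third row:
- Cut 0: 0.95 × 0.15 = 0.1425 against 0.80 × 0.15 = 0.120; OR 0.1662/0.1364 = 1.22.
- Cut 0–1: 0.3325 against 0.280; OR 0.498/0.389 = 1.28.
- Cut 0–2: 0.5225 against 0.440; OR 1.094/0.786 = 1.39.
- Cuts 0–3, 0–4 and 0–5: OR 1.00.

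The fitted 1.20 is a compromise between these values.

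**Step 4: sensitivity to the assumptions.** A second set was used: mRS 20/25/20/15/10/4/6%, with pre-stroke mRS 2, 3 or 4 equally likely among disabled children. A true OR of 1.7 becomes 1.66, 1.62 and 1.55 at 5%, 10% and 20%; a true 2.5 becomes 2.38, 2.27 and 2.08. Under no effect, 10% versus 5% gives 1.08, 20% versus 5% gives 1.27, and 5% versus 20% gives 0.79. The pattern is the same.

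**The case against.** **It may be in the analysis plan.** The article is short, and covariates and sensitivity analyses commonly sit in an SAP that is not shown. The odds-ratio scale does not rule out an adjusted model. This is fair, and it limits the point to what the article fixes: a raw endpoint, open eligibility, non-randomised groups and outcome comparisons that are all unadjusted as stated. Adjustment would be an improvement on that stated analysis. The finding does not show that adjustment has been rejected.

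**Open eligibility is deliberate.** The registry wants to learn about vulnerable subgroups, so admitting children with prior disability fits its purpose. This stands. The remedy leaves eligibility alone.

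**The larger figures are confounding.** The null odds ratios of 1.20 and 0.84 come entirely from unequal groups. The article supports neither the size nor the direction of such an imbalance, and at 10% versus 5% the bias is only 1.06. This stands too. The part that would remain under perfect balance is the modest attenuation.

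**Three stronger readings that the article does not support**
- A reader might infer that disabled children count as poor outcomes whatever treatment does. That would need a good/poor cut-off. The hypothesis in the Introduction says that "MT is safe and results in a high rate of good clinical outcomes compared to the best medical treatment", but no mRS cut-off is defined, and the shift analysis still responds above the floor (70% to 82% in Step 1).
- A reader might infer that the pre-stroke mRS is not used at all. As a baseline characteristic it falls under the planned summary tables and group comparisons, where an imbalance would be visible. It is unused only in the endpoint and the outcome comparison as stated.
- A reader might infer from the item's label that sites will enter the acute score. The bracket says what is meant, acute severity has its own item (PedNIHSS), and the entry form is not shown. Only a clarification of the label is justified.

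**Conclusion.** The point holds in a limited form. As stated, the primary comparison makes no allowance for pre-stroke disability in non-randomised groups with no eligibility limit on it, although the needed variable is collected. If prior disability is equally common in both groups, the harm is modest: a true OR of 2.0 is read as 1.95 to 1.83 at an assumed 5–20% prevalence of pre-stroke mRS 3. If it is unequal, the bias can favour either treatment: null ORs of 1.06 at 10% versus 5% (medical versus MT), 1.20 at 20% versus 5%, and 0.84 when the latter is reversed.

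These sizes rest on assumed prevalences, an assumed mRS distribution and the rule that the day-90 score is the larger of the two components. The existence of the floor and the two-way direction of the bias do not depend on the particular values.

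**What to change.** 1. State that the primary shift analysis is an ordinal model that adjusts for, or is stratified by, pre-stroke mRS. In the illustration an additive term removes the bias from this imbalance (null OR back to 1.00) but only about 40% of the attenuation. Letting each pre-stroke level have its own thresholds would recover more, since the OR above the floor is still 2.0, but some levels may hold too few children. Neither deals with other differences between the groups.
2. Add a sensitivity analysis limited to children with pre-stroke mRS 0–1. It removes the floor from prior disability of mRS 2 or more, at the cost of a somewhat smaller sample.
3. As a minor clarification, label the admission item as pre-stroke mRS, meaning status before this stroke.

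The cost is one covariate already collected, one extra analysis and one label. No new visit or data item is needed, and eligibility stays as it is.
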